### Subgroup and exploratory analyses

Pre-specified exploratory subgroup analyses will be conducted based on treatment progression, disease progression (including opportunistic infections), and adherence levels. These analyses will be interpreted cautiously. All tests will be two-sided with a significance level of p < 0.05 for the primary endpoint. Analyses will be performed using RStudio (Version 2024.12.1 + 563).

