#### Participant characteristics for the clinical trial.

Individuals have been diagnosed as people living with HIV (PLHIV) as per the National AIDS Control Organization (NACO) guidelines. Eligible participants must have a recent CD4 lymphocyte count of at least 350 cells/mm³ (measured within the last 3 months), and HIV RNA viral load performed within 6 months below 50 copies/ mL (TND-Target Not Detected). A Karnofsky performance scale of more than 70 and receiving standard antiretroviral therapy (ART) ≥ 6 months with no planned ART changes, provided by the National AIDS Control Organization (NACO) or an equivalent recognized body. Additionally, they must undergo regular clinical follow-ups (at least 1 visit in the last 3 months) at the ART Clinic, AIIMS, New Delhi.

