### Eligibility criteria

The subjects will be screened from the ART Clinic, AIIMS, New Delhi, based on the following inclusion and exclusion criteria.

Inclusion criteria:

aAdult diagnosed with HIV RNA, and on stable Antiretroviral therapy.bAge: 18–50 years.cKarnofsky performance scale of more than 70.

Exclusion Criteria:

aHistory of any uncontrolled or unstable major medical condition, including hypertension, diabetes, heart failure, stroke, and apparent opportunistic infection.bUse of medications such as immunosuppressive or immunomodulatory agents other than ART within the past 6 months.cKnown physical disability related to any musculoskeletal, neurological or other condition that contra-indicates moderate physical activity or the specific yoga practices in the protocol.dAny psychiatric conditions mandating drug therapy.ePregnant and lactating women.fPracticing any form of yoga, meditation, or exercise.gIndividuals eligible but unwilling to provide written informed consent.

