13.	Protocol deviations	The program will be tailored to the conditions, characteristics, preferences, progression, and improvements of the participant. Modifications will be made and reported based on the participant’s condition or in case of disease progression during the trial (if any).
14.A	How well – Plan	**Compliance and adherence:** To be compliant with the yoga intervention, every participant must attend at least 27 out of the 36 sessions (75%) Participants will be considered adherent if they attend ≥75% of the scheduled supervised yoga sessions, and the prescribed home-practice minutes as recorded in standardized log-book diaries.
14.B	How well – Actual	Adherence and compliance will be evaluated using class attendance logs, self-reported home practice using log-book, and telephonic calls (every 15 days). Participant’s partners will be invited to join the sessions to enhance their adherence.
15.A	Harms – Plan	Throughout the study, each participant will be closely monitored for any adverse reactions that might result from the yoga intervention, or ART medication and for any signs of disease progression. In the event of adverse reactions or disease progression, the treating physician will use clinical judgement and safety factors to determine whether a participant should continue in the study. Participants will receive proper medical attention and any necessary modifications to the yoga intervention will be implemented in response to disease progression or adverse reactions.
15.B	Harms – Actual	To ensure the safety and wellbeing of every participant in the trial, any adverse occurrences will be recorded, submitted to the ethics committee, and examined.

Detailed description of the yoga intervention using the TIDieR-Rehab (Template for Intervention Description and Replication for Rehabilitation) checklist.

Abbreviations: ART = Antiretroviral therapy; PLHIV = People living with HIV; RPE = Rating of Perceived Exertion; CIMR = Centre for Integrative Medicine and Research.

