### Criteria for dropout or early termination

#### Intervention Completion threshold.

Dropout will be considered if participants attend less than 27 sessions of a total of 36 sessions, being categorized as noncompliant, and will be included in an intention-to-treat analysis (ITT). ITT analysis will include all participants as randomized, regardless of the number of sessions attended, any treatment switches, lost to follow-up due to disease progression (including development of opportunistic infection), or second-line treatment or death. However, such participants will be excluded from the per-protocol analysis. Per-protocol analysis will be limited to participants who meet the adherence threshold, i.e., attending at least 27 sessions.

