### Adverse reactions monitoring

Throughout the study, each participant will be closely monitored and will be recorded for any adverse reactions that might result from the yoga intervention, any signs of disease progression, any ART regimen/ dose adjustments, or treatment interruptions (toxicity, intolerance, adherence issues). All reported or observed events will be clinically reviewed by the clinician to determine causality—classified as ART-related, intervention-related (yoga), related to HIV disease progression, or unrelated. In the event of adverse reactions or disease progression, the treating physician will use clinical judgment and safety factors to determine whether a participant should remain in the study. Participants will receive proper medical attention and any required modifications to their yoga intervention in case of disease progression or adverse reactions. To ensure the safety and well-being of every participant in the trial, any adverse occurrences will be recorded, submitted to the ethics committee, and examined.

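### The exploratory subgroups rest mainly on factors that arise after randomisation, so effects within them are open to selection bias; 'adherence levels' is left ambiguous

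*Protocol article*

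**What the plan says.** Under 'Subgroup and exploratory analyses' the protocol fixes three factors: "Pre-specified exploratory subgroup analyses will be conducted based on treatment progression, disease progression (including opportunistic infections), and adherence levels". It adds: "These analyses will be interpreted cautiously". It names no subgroup defined at baseline.

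Other sections show when these factors arise:

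- **State at entry.** 'Participant characteristics for the clinical trial' requires a CD4 count of at least 350, a viral load below 50, and "receiving standard antiretroviral therapy (ART) ≥ 6 months with no planned ART changes". 'Eligibility criteria' excludes uncontrolled or unstable major conditions, "including hypertension, diabetes, heart failure, stroke, and apparent opportunistic infection".
- **During the trial.** 'Intervention Completion threshold' keeps participants in the intention-to-treat analysis regardless of "any treatment switches, lost to follow-up due to disease progression (including development of opportunistic infection), or second-line treatment or death". 'Adverse reactions monitoring' records, throughout the study, "any signs of disease progression, any ART regimen/ dose adjustments, or treatment interruptions (toxicity, intolerance, adherence issues".
- **Programme adherence.** Table 1 says: "Participants will be considered adherent if they attend ≥75% of the scheduled supervised yoga sessions", together with home practice. The threshold is 27 of 36 sessions.
- **Medication adherence.** This is a secondary outcome, which the 'Hypothesis' section expects yoga to change. The ACTG questionnaire is given at baseline and at each follow-up visit.

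**The concern.** A subgroup comparison keeps the protection of randomisation only if membership is settled before allocation or cannot be influenced by it. If membership depends on what happens afterwards, the yoga and walking participants inside a subgroup need no longer be alike in prognosis. A difference between them can then reflect who entered the subgroup and not what the treatment did.

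That risk is concrete here. The two arms follow different programmes, attendance has a threshold only for yoga, and medication adherence is something yoga is hypothesised to alter. A larger apparent benefit among adherent participants could be reported as a pre-specified finding and read as a dose-response when part or all of it is selection. The exploratory label and the promise of caution guard against over-reading chance results. They do not remove a systematic bias, which a larger sample would not cure either.

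**Working it through.** **1. When each factor is determined**

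| Factor | Evidence in the protocol | Timing |
|---|---|---|
| Disease progression, opportunistic infection | Apparent infection excluded at entry; progression listed among events in randomised participants and monitored throughout | After randomisation |
| Treatment progression | Not defined; stable ART with no planned change at entry; switches and second-line treatment listed as on-trial events | Most naturally after randomisation |
| Adherence: sessions | At least 27 of 36 yoga sessions plus home practice; no matching threshold for walking | After randomisation |
| Adherence: medication during the trial | Secondary outcome, hypothesised to change | After randomisation |
| Adherence: medication at baseline | ACTG questionnaire at baseline | Before randomisation, but the text does not say this is meant |

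**2. The plan's own figures, used as the yardstick**

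'Sample size calculation' gives a difference of 1.54 and an SD of 3.38. 1.54 / 3.38 = 0.456 (stated as 0.455). A two-sided t-test at 5% with 80% power needs 76.8, so 77 per group and 154 in total, as stated. 154 / 0.8 = 192.5, against 192 stated. Nothing in this point changes the sample size.

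**3. Attenders against their whole arm, with no true effect**

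Assumptions, none given in the protocol:

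- The correlation r between propensity to attend and a better 3-month HADS score is 0.2 to 0.3.
- The share s of yoga participants who reach 27 sessions is 75% or 80%. The 80% mirrors the planned 20% attrition, since attending fewer than 27 sessions is classed as dropout. The 75% is a second assumed value and is not the session threshold.
- Propensity and outcome are jointly normal.

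Shift = r × 3.38 × φ(z) / s, where z is the normal quantile that cuts off the top share s.

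- s = 0.80: φ(z)/s = 0.280 / 0.80 = 0.350. Shift = 0.2 × 3.38 × 0.350 = 0.24, and 0.3 × 3.38 × 0.350 = 0.35.
- s = 0.75: φ(z)/s = 0.318 / 0.75 = 0.424. Shift = 0.2 × 3.38 × 0.424 = 0.29, and 0.3 × 3.38 × 0.424 = 0.43.

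The range is 0.24 to 0.43 points, or 15% to 28% of 1.54.

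**4. Yoga against control within the subgroup, with no true effect**

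The between-arm bias depends on how the control arm is split.

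- *Same rate (75%) and same link to prognosis in both arms:* zero among adherers.
- *Assumed rates of 65% yoga and 85% control, same link:* among adherers r × 3.38 × (0.570 − 0.274), which is 0.20 at r = 0.2 and 0.30 at r = 0.3, in yoga's favour. Among non-adherers r × 3.38 × (1.554 − 1.058), which is 0.34 and 0.50, also in yoga's favour. A simulation of 2 million participants gave 0.19 and 0.30, and 0.32 and 0.51.
- *Same 75% rate, but adherence linked to prognosis only in the yoga arm, r = 0.3:* simulation gave 0.44 in yoga's favour among adherers and 1.28 against yoga among non-adherers.

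So a null treatment can look helpful or harmful within a subgroup, depending on the mechanism.

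**The case against.** The strongest reply is that the protocol limits the consequences. The analyses are labelled exploratory, caution is promised, and p < 0.05 is tied to the primary endpoint. The primary comparison is an intention-to-treat ANCOVA that none of this touches. That stands, and it lowers the severity. It does not make the within-subgroup comparisons valid.

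Three further points stand in part:

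- **Wording.** 'Adherence levels' could mean baseline medication adherence, which would be legitimate, and 'treatment progression' has no definition. The text must therefore be clarified, and it cannot be said that all three factors are certainly post-randomisation. The disease-progression factor is not rescued by either reading.
- **Control-arm data.** Both arms keep a logbook covering physical activity and medication, so some measure of adherence exists for the walkers. What is missing is a matching threshold.
- **Rates.** The protocol supplies no correlation or attendance rate, so every bias figure is an illustration.

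A reader might be tempted to go further in three ways that the protocol does not support. First, that subgroup effects will be biased and an adherence effect would be bound to appear even if yoga did nothing: the bias is close to zero when adherence rates and links to prognosis match across arms. Second, that the shift is 0.54 to 0.81 points: that comes from splitting the yoga arm at its median, whereas the protocol's cut is 27 of 36 sessions, and it is not a comparison between arms. Third, that the progression subgroups will be nearly empty: this is plausible in a stable population, but no event rate is given.

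**Conclusion.** The point holds in a limited form. The disease-progression factor is post-randomisation on the protocol's own account, treatment progression most naturally is, and adherence is unless baseline medication adherence is meant. Effects estimated within post-randomisation groups are open to selection bias of unknown size and direction.

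Under the stated assumptions, yoga attenders would look 0.24 to 0.43 HADS points better than their whole arm with no true effect. This is not negligible against a design difference of 1.54, but it is well short of it. Between arms it would be smaller if both are split in the same way, and could be larger or change sign if adherence relates to prognosis differently in the two arms.

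The primary analysis and sample size are unaffected. Severity is low to moderate.

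**What to change.** Before recruitment starts:

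1. Remove disease progression, treatment progression and on-trial adherence as subgroup factors.
2. Define any subgroups by baseline variables already collected, and test each by a treatment-by-subgroup interaction in the primary ANCOVA. Examples are baseline HADS at the protocol's cut-off of 8, or baseline medication adherence. Before using self-reported adherence, correct the formula under 'Medication adherence': as printed, zero missed days gives (1 − 0) / 30 × 100 = 3.3%, so a 95% cut would not work.
3. Report progression, opportunistic infection and adherence descriptively by arm.
4. If an effect of programme adherence is wanted, state a causal estimand, its assumptions, and a compliance definition for both arms. A complier-average analysis cannot simply be carried over, because the comparator is itself an active walking programme.

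The cost is a change of wording, with no added visits, measurements or participants. The downside is that the planned look at progressors and adherers as subgroups is lost. Baseline adherence below 95% may also prove sparse in participants selected for viral suppression, though the protocol gives no rate.

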#### Hypothesis.

The primary hypothesis to be tested is that yoga therapy as an adjunct therapy will lead to a change in depression and anxiety scores among PLHIV on ART therapy as compared to an active control (moderate-to-intensity walk). The secondary hypothesis included that a yoga therapy would lead to changes in all secondary health outcomes and would produce significant changes in medication adherence among PLHIV on ART therapy, as compared to an active control (moderate-to-intense walk).

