#### Description of the outcome measures.

The study will begin with a baseline screening visit, during which written informed consent will be obtained before starting any additional study activity. Clinical assessment, medical history, demographic characteristics, and questionnaire data will be collected at baseline and at the 3rd, 6th, and 12th-month follow-up visits. After being fully rested, all assessments will be conducted in the following order: heart rate, blood pressure, body composition, and questionnaires (Hospital Anxiety and Depression Scale (HADS), WHOQOL-HIV BREF, SF-36, Perceived Stress Scale, and the ACTG Adherence Baseline & Follow-Up Questionnaire). The primary endpoint is the change in anxiety and depression scores (HADS-A and HADS-D) from baseline to 3 months. All secondary endpoints will be assessed at baseline, 3 months, 6 months, and 12 months.

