### Primary outcome measure

#### Hospital anxiety and depression scale (HADS).

In 1983, Zigmond and Snaith created the widely used Hospital Anxiety and Depression Scale (HADS), a self-assessment tool, to identify whether patients in non-psychiatric hospitals or clinics, potentially or probably have anxiety disorders or depression. The scale comprises 14 items divided into two subscales: the HADS-A (Anxiety Subscale), with 7 items assessing anxiety symptoms, and the HADS-D (Depression Subscale), with 7 items assessing depression symptoms. The scale has cut-off points for classifying symptom severity: 0–7 is normal, 8–10 is borderline abnormal (mild), and 11–21 is abnormal (moderate to severe). This tool has strong internal consistency for both measures in HIV population, with a Cronbach’s alpha of 0.83 and 0.84 for the anxiety subscale and depression subscale respectively [28].

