### Sample size calculation

The sample size was determined based on a previous study, taking into account an expected mean difference of 1.54 and a pooled standard deviation of 3.38 [36]. The sample size is calculated for a two-sided independent-samples t-test to detect a standardized effect size (Cohen’s d) of 0.455, with a two-sided significance level α = 0.05, power 80%, and equal allocation (N₂/N₁ = 1). The required sample size is 154 participants (77 per group). After accounting for a 20% attrition rate, the adjusted sample size is 192 (96 participants per group).

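### HADS-A and HADS-D are both primary, but the protocol gives one alpha and one single-test sample size and does not say whether one or both must be significant

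*Protocol article*

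**What the plan says.** All references are to the protocol article.

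- **Endpoint** (Description of the outcome measures): "The primary endpoint is the change in anxiety and depression scores (HADS-A and HADS-D) from baseline to 3 months". The abstract lists the same two scores as the primary outcome.
- **Instrument** (Hospital anxiety and depression scale): "The scale comprises 14 items divided into two subscales", one for anxiety and one for depression, with 7 items each. No HADS total score is named as primary.
- **Hypothesis**: "yoga therapy as an adjunct therapy will lead to a change in depression and anxiety scores among PLHIV on ART therapy", compared with the walking control.
- **Analysis** (Statistical analysis): an ANCOVA of the 3-month value on treatment group and the baseline value of that outcome. It is written for one dependent variable. Secondary outcomes are exploratory.
- **Significance level** (Subgroup and exploratory analyses): "All tests will be two-sided with a significance level of p < 0.05 for the primary endpoint".
- **Sample size** (Sample size calculation): "an expected mean difference of 1.54 and a pooled standard deviation of 3.38", for a "two-sided independent-samples t-test to detect a standardized effect size (Cohen’s d) of 0.455" at two-sided 0.05 and 80% power. This gives 77 per group, or 154 in all, and 192 after 20% attrition. The subscale to which the difference and SD belong is not named.

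The article contains no alpha split, testing order, composite, or statement that one or both subscales must be significant.

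**The concern.** Two separately scored subscales, each with its own ANCOVA, give two p-values. The article speaks of one primary endpoint, one significance level and one power, so it does not say how the two p-values combine into a conclusion. If one subscale is significant and the other is not, the trial could be reported as a success or as a failure, and the choice could be made after the results are known.

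The article itself makes a split result foreseeable. Its Introduction cites a meta-analysis in people living with HIV that found a significant yoga effect on anxiety and none on depression. Since the secondary outcomes are exploratory, this is the trial's only confirmatory claim.

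The rule also determines what the stated figures mean. Accepting either subscale puts the 5% error rate at risk. Requiring both puts the 80% power at risk.

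**Working it through.** **Inputs from the article:** difference 1.54, SD 3.38, two-sided alpha 0.05, power 80%, 77 per group evaluable, analysis by ANCOVA with the baseline value as covariate.

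**Assumptions, because the article gives no figure:** correlation *r* between the HADS-A and HADS-D test statistics, 0 to 0.8; correlation ρ between baseline and 3 months; the same standardized effect on both subscales; 3.38 is the raw (not baseline-adjusted) SD.

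**1. The plan's own figure.** d = 1.54/3.38 = 0.456. The exact (noncentral t) calculation needs 76.6 per group, so 77, with 80.2% power. 154/0.8 = 192.5, against 192 stated. The single-test calculation is right.

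**2. Either subscale suffices, each tested at 0.05.** Family-wise error = 1 − P(|Z₁| < 1.96 and |Z₂| < 1.96), which is 1 − 0.95² = 0.0975 under independence and comes from the bivariate normal otherwise. Power for at least one = 2 × single-test power − joint power.

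**3. Both subscales required, each at 0.05.** The chance of a false claim cannot exceed that of one test, so error stays at or below 5%. Joint power under independence is 0.802² = 0.643 with the exact single-test power. The normal approximation (single-test power 0.807) gives 0.651. Other values come from the bivariate normal. Ranges show the two methods.

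| *r* | Family-wise error, either | Power for at least one | Joint power, both |
|---|---|---|---|
| 0 | 9.75% | 96% | 64–65% |
| 0.5 | 9.1% | 91–92% | 69–70% |
| 0.8 | 7.8% | 87–88% | 73–74% |

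**4. Effect of the planned ANCOVA.** Adjustment for baseline raises the effective d to d/√(1 − ρ²). For example, at ρ = 0.5 it is 0.456/0.866 = 0.526, and single-test power at 0.05 is 90.0%. With 77 per group:

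| ρ | Joint power at 0.05 each (*r* = 0 to 0.8) | Power for one subscale at 0.025 |
|---|---|---|
| 0 (t-test basis) | 64–74% | 71% |
| 0.3 | 70–78% | 76% |
| 0.4 | 75–81% | 79% |
| 0.5 | 81–86% | 84% |

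The 0.025 column is the level that the smaller p-value must meet under Holm. The chance that at least one of two equally affected subscales passes 0.025 is higher: 92% to 81% for *r* = 0 to 0.8, on the t-test basis by the normal approximation.

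The ANCOVA does not change the family-wise error in step 2.

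**The case against.** **The wording points to both.** The hypothesis joins depression and anxiety with an *and*. Its most literal reading is that both must change, and then 0.05 on each needs no adjustment. This stands as a reading, but the article never states it as a rule. Nor does it state that each subscale is tested at 0.05. That is an inference from a level set for a singular endpoint, though no other level is offered.

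**The power shortfall rests on a test that will not be run.** This stands in part. The article bases its 80% on an unadjusted t-test but plans an ANCOVA. With a baseline correlation of about 0.5, joint power exceeds 80% at every subscale correlation considered. At 0.3 it does not. The article gives no correlation, so the shortfall is conditional.

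**The extremes are bounds.** Independence of two subscales of one questionnaire is unlikely, so the 9.75% error and the 64% joint power are limits. At a correlation of 0.8 the figures are 7.8% and about 73–74%.

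**Multiplicity is often left to the analysis plan.** That would answer a mere omission. Here the article does fix the alpha, the power and the sample size, and fixes them for one test while naming two primary outcomes.

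**A stronger reading is tempting.** A reader might infer that neither the 5% error rate nor the 80% power holds. The documents do not support that, because the two losses belong to mutually exclusive rules. Under *either*, error rises but power for at least one is 87–96%. Under *both*, error is controlled and only power can fall short.

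**Conclusion.** The point holds as a missing decision rule for the trial's one confirmatory claim, with a stated alpha and sample size that fit a single test. This does not depend on any assumed correlation.

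Its numerical consequence depends on the rule:

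- **Either subscale:** family-wise error of about 8–10%, for an assumed subscale correlation of 0.8 to 0.
- **Both subscales:** joint power of about 64–74% on the stated t-test basis, with the same effect on each. The ANCOVA may or may not bring it back to 80%, depending on a baseline correlation that the article does not give.

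The single-test sample size calculation is correct, and the estimates and 95% intervals for each subscale are unaffected. The point should be settled before unblinding, because the rule can decide whether a split result counts as a success.

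**What to change.** State one rule in the protocol, the analysis plan and the registry entry before unblinding:

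- **Holm:** HADS-A and HADS-D are two primary outcomes, tested at family-wise two-sided 0.05. The smaller p-value is compared with 0.025 and, if it passes, the other with 0.05.
- **Both required:** success means significance on both subscales at two-sided 0.05 each, with no adjustment.

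With either rule, name the subscale from which 1.54 and 3.38 come, say whether 3.38 is a raw SD, and give the effect assumed for the other subscale. Restate the power for the chosen rule under the planned ANCOVA, with its assumed baseline-to-3-month correlation.

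The cost is a few sentences and a registry update. No extra patients are needed if the restated power is accepted, but it may be less favourable than the 80% now stated.
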